## Methods

### Study design, steering committee, and participating centers

This is a multicenter, international, non-competitive, observational two-segment study.

The study segments include a first one with retrospective patient enrollment and a second one with prospective enrollment (Table 3).

**Table 3 Tab3:** Study design and population

	Prospective segment (high-volume centers ≥ 65 transplants per year)	Retrospective segment (low- & intermediate- volume centers < 65 transplants per year)
Sample size	750	4200
Consecutive pts to be included	50	75
No. of Centers to be involved	15	56
Enrollment period	July ‘21–December ‘23	January ‘17–December ‘19
Data entry period	Up to January’25 (follow-up)	Up to October’24 (follow-up)
AIMs	Development/validation of NEW/previous prognostic algorithms	Validation of previous kinetic algorithms
Main parameters	AST, PLT, BIL, INR	AST, PLT, BIL, INR
Outcome data and follow-up	Incidence of AF at 90 and 365 days Comprehensive complication index Length of stay in ICU, length of stay in hospital 90d and 365d graft survival, 90d and 365d patient survival, 90d and 365d ischemic cholangiopathy-free survival Actuarial data at 12 months	Incidence of AF at 90 and 365 days Comprehensive complication index Length of stay in ICU, length of stay in hospital 90d and 365d graft survival,90d and 365d patient survival, 90d and 365d ischemic cholangiopathy-free survival Actuarial data at 48 months
Pre-operative assessment	Yes	No
Sarcopenia		Yes
Malnutrition		Yes
Cardiac risk		Yes
Renal risk		Yes
Biopsy of the graft (back table)	DBD, DCD	Only when available
Post-operative assessment of factors that favour or contraindicate re-transplant	Yes	No
Number of parameters to be recorded	297	241
Number of calculated fields	27	24

Prospective and retrospective segments

A steering committee (SC) was constituted to design the study (Fig. 1). Members were identified according to their experience on the topic and their geographic area (Europe, Americas, and Asia).

**Fig. 1 Fig1:**
[figure not shown]
International Steering Committee

Responsibilities of the SC are:to select and invite other LT centers in each SC member’s geographic area;to supervise on the thoroughness of the data collection;to evaluate the robustness of the study results and make decisions on the divulgation and publication policies.

A draft of the preliminary study design and subsequent questionnaires on controversial issues were circulated among members.

Controversial issues were solved through discussion among SC members during online meetings.

The GANTT diagram of the study is illustrated in Fig. 2.

**Fig. 2 Fig2:**
[figure not shown]
GANTT diagram

The team leaders of participating centers amended the manuscript according to local logistical conditions, allowing a common list of parameters to be collected.

### Setting

The study will be conducted in 60 (or more) liver transplant centers representative of the global liver transplant activity (Fig. 2). The Italian liver transplant population constitutes the primary study population, while the other geographic areas (Europe without Italy, Asia, Oceania, and North and South America) will be used as a comparator. Instead, for the development of the main algorithms, the study population will be utilized as a whole.

Since the study aims to reflect the worldwide liver transplant activity, to balance each country contribution in the study, we used the proportions of LT activity as reported on the Global Liver Transplant Observatory [32]. This ranks the yearly number of transplants performed in various countries in decreasing order. A stratification of all cases in five classes based on quintiles was provided to parallel the number of centers to be recruited in each country. For countries in the 4^th^ and 5^th^ quintile classes, one or two centers are allowed, coherently with the 75 cases per center rule (Fig. 3), as per participation in the “Retrospective segment” of the study. Countries with < 50 cases per year are not considered.

**Fig. 3 Fig3:**
[figure not shown]
Rank of countries according to liver transplant activity and rank of enrolled transplants

The study will be structured in two segments, based on the enrollment modality: prospective and retrospective. Two distinct data collections will be created accordingly.Prospective segment. Seven hundred fifty liver transplant recipients will be enrolled in 15 high-volume centers (defined as performing ≥ 65 LT a year on average during the 2017–2019 period). Each center will enroll 50 consecutive transplants from July 2021 to December 2023 according to the inclusion criteria. For each transplant, a further 365 days will be necessary for the minimum follow-up.Retrospective segment. A retrospective data collection was conceived for medium–low volume centers (defined as performing < 65 LT a year), to participate in the study using the data of LTs performed between December 31, 2019, and January 1, 2017 (75 cases backward enrollment).

High-volume centers participating in the prospective segment will be allowed to enroll patients in the retrospective segment, too, voluntarily, thus enrolling 125 transplants (50 prospective and 75 retrospective transplants).

Inclusion and exclusion criteria are depicted in Table 4.

**Table 4 Tab4:** Inclusion and exclusion criteria

Inclusion criteria
1. Adult cases (≥ 18 years) 2. First transplant (retransplants to be enrolled when first transplant enrolled) 3. DBD grafts 4. DCD grafts (controlled and uncontrolled) 5. DBD and DCD grafts managed by perfusion machines 6. Living donor grafts (both left lobe and right lobe grafts) transplanted into adult recipients 7. Split liver grafts (both left lobe and right lobe grafts) transplanted into adult recipients
Exclusion criteria
1. Combined grafts (e.g., liver-kidney, liver-heart, liver-pancreas, multi-visceral grafts) 2. Domino grafts 3. Heterotopic grafts 4. Double grafts 5. Cholangiocarcinoma 6. Colorectal liver metastases

Due to some concerns regarding the differences in the prevalences of AB0 incompatible grafts among different countries, these patients can be enrolled concurring to the target number of cases for each center. During the statistical analysis, we will evaluate the opportunity to include them or not in the study population, being aware of the substantial equivalence in the survival results

The software of the eCRF will check the fulfillment of the eligibility criteria and whether the target number of cases for each Center has been reached

We expect to enroll approximately 5000 patients (750 from the prospective segment and at least 4200 from the retrospective segment) (Table 5).

**Table 5 Tab5:** List of participating Centers

**Italy** Fondazione Policlinico Universitario Agostino Gemelli, IRCCS; Rome, Italy Ancona hospital; Ancona, Italy AOU Policlinico consorziale di Bari; Bari, Italy ASST Papa Giovanni XXIII; Bergamo, Italy Azienda Ospedaliero-Universitaria, Policlinico di Sant'Orsola; Bologna, Italy University of Milan and National Cancer Institute, IRCCS; Milan, Italy University of Milano-Bicocca and Niguarda-Cà Granda Hospital; Milan, Italy Fondazione Cà Grande Ospedale Maggiore Policlinico, IRCCS; Milan, Italy University of Modena and Reggio Emilia; Modena, Italy Azienda Ospedaliera A. Cardarelli; Naples, Italy ISMETT IRCCS – UPMC; Palermo, Italy Azienda Ospedaliera Universitaria; Padova, Italy University of Pisa Hospital; Pisa, Italy Azienda Ospedaliera San Camillo Forlanini; Rome, Italy Sapienza University; Rome, Italy University of Rome Tor Vergata; Rome, Italy Città della Salute e della Scienza; Torino, Italy Università di Udine – ASUFC; Udine, Italy University Hospital Trust of Verona; Verona, Italy
**Europe except Italy** Cliniques Universtaires Saint-Luc; Louvein, Belgium Croix-Rousse University Hospital, Hospices Civils de Lyon; Lyon, France Beaujon Hospital, Université Paris Cité; Paris, France Regional University Hospital; Tours, France University Hospital Schleswig–Holstein; Campus Kiel, Germany Universitätsklinik Tübingen; Tubingen, Germany Erasmus University Medical Center; Rotterdam, Netherlands Surgical National Medical Research Center of Transplantation and Artificial Organs named after V.I. Shumakov, Moscow, Russia Public Central Teaching Hospital, Medical University; Warsaw, Poland University of Barcelona; Barcelona, Spain Hospital Universitario Cruces-Bilbao; Bilbao, Spain Clintec Karolinska University Hospital; Stockholm, Sweden Ankara University; Ankara, Turkey Queen Elizabeth Hospital; Birmingham, UK Newcastle Hospital NHS Foundation Trust; Newcastle, UK

### Study main steps

Creation of the study protocol and feasibility analysis (i.e., IRB approval, possibility to collect data, and resources allocation).Acquisition of epidemiological data: a snapshot of the liver transplant activity in the different countries of the world.Data analysis, development, and validation of prognostic algorithms.Divulgation.

### Ethics and authorisations

The Ethics Committee of Fondazione Policlinico Universitario Agostino Gemelli (id 4571), Rome, and the Institutional Review Board of the University of California, Los Angeles, (respectively, the affiliations for [name], principal investigator, and for [name], co-principal investigator) approved the study design and the provisional study protocol. The provisional study protocol was submitted to the European Society of Organ Transplantation (ESOT), the International Liver Transplant Society (ILTS), the American Association for the study of liver disease (AASLD), the American Society of Transplantation (AST), and the Asian Society of Transplantation (AST) for suggestions and promotion among the Liver Transplant centers. The amended protocol was circulated again among the steering committee members for approval. Finally, the members submitted the study protocol to the local institutional review boards for approval.

No modification to the participating centers’ standard practice for managing LT donors and recipients is required. The study was structured according to the Guidelines for Strengthening the Reporting of Observational Studies in Epidemiology (STROBE) [33].

The study was registered on clinicaltrials.gov (NCT05289609).

### Outcome measures

Allograft failure (AF) was defined as graft failure (leading to retransplant or death) for any reason at day 90 and at day 365 after LT. This definition also captures all late-occurring AFs (also known as delayed non-function) [34, 35] We consider as AF determinants all those events potentially affecting the process of graft function recovery, independently if they were strictly associated with ischemia–reperfusion injury. Indeed, vascular (thrombosis of the hepatic artery or portal vein), biliary, toxic, and major hemodynamic events will be included, because any of them can interact with parenchymal dysfunction, affecting graft function recovery and favoring graft failure and death.

Other outcome measures are comprehensive complication index, intensive care unit length of stay, hospital length of stay (LoS), and cholangiopathy-free survival at 90 and 365 days, graft and patient survival at 90 and 365 days,

The prospective cohort dataset includes 297 data entries and 27 calculated parameters (see supplementary material 1). Variable domains are:identification datadonor characteristics datarecipient preoperative datagraft histology dataintraoperative datarecipient postoperative datastudy endpoints dataoutcome and follow-up data.

The electronic Case Report Form (eCRF) was developed using the REDCap ver 10.0.21 software hosted at https://redcap-irccs.policlinicogemelli.it/. The eCRF allows easy calculation of scores including L-GrAFT and EASE scores.

The REDCAP software performs de-identification and encryption of the data.

The retrospective segment dataset includes 241 variables (supplementary material) to be collected from each center’s previously existing databases.

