## Introduction

During the last decade, the expansion of the donor pool using extended criteria (ECD) and donation after cardiocirculatory death donors (DCD) has resulted in heightened attention to allograft failure (AF) due to ischemia–reperfusion injury after liver transplantation (LT). The prompt diagnosis of AF is paramount to defining the indication for early retransplantation. Moreover, the grafts from ECD and DCD may develop early AF during the initial 90 days [1, 2] and delayed AF, primarily due to ischemic cholangiopathy [3]. LT from living donors (LDLT) is a growing procedure worldwide. However, the prevalence of steatosis in the general population is growing, too. A safety threshold for graft steatosis has yet to be entirely investigated, and the possible role of mitigation strategies to reduce the risk of AF in LDLT is a critical unmet need.

The evaluation times and the modalities to promptly identify AF are still the object of research. No consensus exists on the most accurate predictors and indicators of AF, neither on potential mitigation strategies [4–11]. In addition, ECD and DCD grafts are burdened by a higher incidence of ischemic cholangiopathy [12], which typically develops after 6–12 months, which is also a cause of AF and need for retransplantation. With the intent to further expand and optimize the donor pool, machine perfusion (MP) technologies are increasingly employed, allowing utilization of organs that have traditionally been discarded. Moreover, MP allows extended preservation times and assessment of graft viability, especially when considering organs with multiple risk factors (e.g., elderly donors, steatotic grafts, post-anoxic grafts, etc.). [13]

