Secondary (#5)	To identify the best-time for re-transplant (after stratification according to the post-operative weeks, months, trimesters);
Secondary (#6)	To investigate differences in the incidence of allograft failure and ischemic cholangiopathy at 90 and 365 days according to standard DBD, DCD and high- risk DBD, LD donor grafts;
Secondary (#7)	To evaluate the effect of mitigation strategies on the precipitating factors of Allograft Failure at 90 and 365 days;
Secondary (#8)	To investigate the association of kinetic algorithms with development of post- LT complications (acute kidney injury, ischemic cholangiopathy, other complications);
Secondary (#9)	To identify risk factors for mortality that may contraindicate re-transplant;
Secondary (#10)	To investigate the impact of donor-to-recipient gender match on LT outcomes

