### Variables and statistical analysis plan

#### Qualitative variables

All variables will be first explored by missing analysis at three levels: at center level; at country level; at geographic area level.

Histology obtained at the back-table graft preparation, or alternatively at any time before graft implantation, will constitute a key point although not a mandatory condition for the enrollment. The histology slides will be scanned at the local centers, de-identified and uploaded on the eCRF, and centrally read for research purposes.

Transplant candidates CT scan (DICOM files only) from the pre-listing work-up will be de-identified and uploaded on the eCRF and centrally read for research purposes.

The incidence and grade of ischemic cholangiopathy will be measured by means of a cholangio-MR at 10–12 months after LT (on-demand, based on clinical suspicion of ischemic cholangiopathy for all grafts, e.g., higher than twofold increase in baseline alkaline phosphatase levels). The DICOM files will be anonymised and uploaded on the eCRF and centrally read for research purposes.

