Kaplan–Meier curves will be calculated and differences will be investigated through log-rank test.ii.Missing data management.

A. Missing data in the calculation of the area under the curve (AUC) and the slope of the kinetic model will be addressed as follows:Patients who were retransplanted or died before day 10 were excluded from the calculation of the AUC and slope because of the real impossibility to calculate the score which is by definition computed at day 10. The number of this subgroup will be reported in the flow diagram of the patients. These cases will be excluded from the patient population utilized for the development of algorithms. However, these cases will be considered for the calculation of the outcome measures (overall % of AF, % failure at 90 days, % failure at 365 days, length of stay, overall graft survival, and overall patient survival).Patients who have been discharged between day 8 and 10 and do not have the day 10 determination (missing value referring to the day 10 determination of AST or Platelet count or bilirubin). In these cases, the values at day 7 will be used. The number of these cases will be reported in the flow diagram. We are aware that this approach might overestimate the value of the AUC and consequently the score’s value. However, as the number of patients without day-10 data is expected to be small, we believe that the effect will be minimal and not relevant for the purpose of the study.Patients with missing data at day 2, or day 3 will be excluded, being impossible the calculation of the score. Their number will be reported in the flow diagram.Patients with missing data at day 4 will be included. The AUC and the slope will be calculated using the trapezoid method not including day 4. Their number will be reported in the flow diagram.Patients with missing data at day 5 will be included. The AUC and the slope will be calculated using the trapezoid method not including day 5. Their number will be reported in the flow diagram.Patients with missing data at day 6 will be included. The AUC and the slope will be calculated using the trapezoid method not including day 6. Their number will be reported in the flow diagram.Patients with missing data on two consecutive days (day 4 and 5, or day 5 and 6, or day 6 and 7) will be included. The AUC and the slope will be calculated using the trapezoid method not including the two consecutive missing days. Their number will be reported in the flow diagram.Composite missing data (e.g., AST from one day and bilirubin from a different day) will follow the above-mentioned rule. Their number will be reported in the flow diagram.Missing data in the descriptive analysis will be reported. Parameters of interest with percentage of missings higher than 8% will not be reported in tables neither will be considered for further univariate or multivariate analysis.Loss to follow-up.

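### Objective #6 asks for the incidence of ischemic cholangiopathy, but the outcome lists name only cholangiopathy-free survival, a different quantity that on its usual reading can separate graft types through death or graft loss alone

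*Protocol article*

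**What the plan says.** Three parts of the protocol article describe the IC endpoint, and they do not describe the same quantity.

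- **Objective.** Table 2, secondary #6: "To investigate differences in the incidence of allograft failure and ischemic cholangiopathy at 90 and 365 days", by donor graft category.
- **Outcome lists.** Outcome measures lists "cholangiopathy-free survival at 90 and 365 days". Table 3 lists "90d and 365d ischemic cholangiopathy-free survival" for both segments. Neither list includes the incidence of IC.
- **Measurement.** Qualitative variables: "The incidence and grade of ischemic cholangiopathy will be measured by means of a cholangio-MR at 10–12 months after LT", with the scan "on-demand, based on clinical suspicion of ischemic cholangiopathy for all grafts".

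The Statistical analysis plan section says that incidences at 90 and 365 days will be calculated for AF and for death. It does not name IC there. It provides a chi-square test for qualitative variables, Cox models for AF risk factors, and this general sentence: "Kaplan–Meier curves will be calculated and differences will be investigated through log-rank test". No competing-risks method is mentioned. Definitions are referred to supplementary material 2, which is not shown.

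**The concern.** Incidence of IC counts patients who develop IC. IC-free survival, as the term is ordinarily used, counts patients who develop IC or die, and sometimes those who lose the graft for any reason. A graft type with more early deaths does worse on the second measure even if its bile ducts are unaffected.

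This matters here for two reasons. First, the protocol itself expects AF (retransplant or death from any cause) to differ by donor category. Second, the Introduction says of IC "which typically develops after 6–12 months", so few IC events can be expected by day 90. A 90-day comparison of IC-free survival would then largely repeat the comparison of early death or graft loss, and a difference could be reported as an answer to the IC objective.

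**Working it through.** The documents give no rate, sample size or power for IC, so there is no stated figure to reproduce. The calculations below only illustrate size.

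**Inputs from the protocol.** AF hypotheses (Study size and power calculations): living donor 4%, standard deceased donor 7%, high-risk deceased donor 10%. No time point is attached to them; they follow a list of mostly 90-day rates. Significance level 0.05.

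**Assumptions.** Share of AF that are deaths, group sizes, IC rates, IC onset day and the total of competing losses.

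**Step 1: IC-free survival with no IC.** IC-free survival = 1 − P(death or counted graft loss).

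| | Living | Standard | High-risk |
|---|---|---|---|
| True IC incidence | 0% | 0% | 0% |
| All AF counted | 96% | 93% | 90% |
| Half of AF are deaths, only deaths counted | 98% | 96.5% | 95% |

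The spread is 6 percentage points in the first case and 3 in the second, none of it IC.

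**Step 2: chance of a significant result with no IC.** Two-sided 0.05, comparing p₁ = 2% (living) with p₂ = 5% (high-risk), n₁ = 500, n₂ = 1000.

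- Unpooled SE = √(0.02×0.98/500 + 0.05×0.95/1000) = 0.00931. Power = Φ(0.03/0.00931 − 1.96) = 0.90.
- Pooled p = (10 + 50)/1500 = 0.04. Pooled SE = √(0.04×0.96×(1/500 + 1/1000)) = 0.01073. Power = Φ((0.03 − 1.96×0.01073)/0.00931) = 0.83.

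Other cases:

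- 2% v 5%: 73% at 500 per group and 37% at 200 per group.
- 4% v 10% (all AF counted): 96% at 500 per group.
- High-risk v standard at 500 per group: 40% (10% v 7%) or 22% (5% v 3.5%).

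**Step 3: IC as the only event, with death and retransplant censored in Kaplan–Meier.** Daily model for a high-risk group. In the absence of IC, competing losses reach 10% by day 90 and 15% by day 365. The IC hazard is zero to day 150 and constant afterwards. Cumulative incidence = Σ S(d−1)·h(d), where S is the chance of being alive in the first graft without IC; 1 − KM = 1 − Π(1 − h(d)).

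| True cumulative incidence | 1 − KM | Excess in SE, n = 500 | Excess in SE, n = 1500 |
|---|---|---|---|
| 3% | 3.45% | 0.6 | 1.0 |
| 6% | 6.9% | 0.8 | 1.5 |
| 10% | 11.5% | 1.1 | 1.9 |

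Here SE = √(p(1−p)/n) at the true incidence p. In the 10% row, 1 minus IC-free survival with every loss counted is 24.8%.

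**Step 4: does the measurement passage supply the incidence?** A scan at 10–12 months cannot give a 90-day incidence. Patients who died or were retransplanted before it have no scan in that window, and the text shown does not say how they are classified.

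**The case against.** The strongest defence is that an incidence route already exists. Qualitative variables says that incidence and grade will be measured, Quantitative variables looks at non-anastomotic biliary complications by graft type, and the analysis plan offers a chi-square test for qualitative variables. If every patient has 365 days of follow-up, the Aalen–Johansen estimate at day 365 equals the crude proportion with IC, so the proposed method would add little. This part stands: it would be wrong to say that cholangiopathy-free survival is the only IC measure in the protocol, or that no valid incidence could be computed. It does not close the gap, because the proportion is not stated for IC at 90 and 365 days, the scan falls at 10–12 months on suspicion, and grafts lost earlier are not addressed.

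A reader might also infer three stronger things that the document does not support:

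- **That the protocol counts deaths as events in cholangiopathy-free survival.** This is the ordinary meaning, but the term is not defined in the text shown, and the supplement may define it.
- **That the protocol plans 1 − KM for IC.** The Kaplan–Meier sentence is general and follows a paragraph on AF and death. Step 3 shows only what would happen if those tools were used on IC with losses censored.
- **That a significant log-rank result would necessarily be misread as a cholangiopathy effect.** Graft and patient survival are listed beside it, so an attentive reader could see deaths driving a difference.

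**Conclusion.** The point holds as a mismatch between a secondary objective and the outcomes listed for it. Objective #6 and the measurement passage speak of incidence; both outcome lists speak of event-free survival. A definition in the supplement could settle how death is handled but would not make the two quantities the same.

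On the usual reading, the protocol's own AF hypotheses alone give a 3 to 6 point spread in IC-free survival between living-donor and high-risk grafts with no IC, and the 90-day version would be almost entirely mortality or graft loss. The chance that this reaches significance depends heavily on the assumed group sizes: about 83–90% at 500 v 1000 for 2% v 5%, but 37% at 200 per group. Overstatement from censoring losses is the lesser issue: 0.45 to 1.5 points under the assumed rates, and only if that analysis is chosen.

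**What to change.** Reconcile Table 2 (#6), Table 3, Outcome measures and Qualitative variables as follows.

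1. For objective #6, list the cumulative incidence of IC in the first graft at 90 and 365 days. Treat death and retransplant for other causes as competing events, and count retransplant because of IC as an IC event.
2. Estimate it by Aalen–Johansen and compare graft types with Gray's test or cause-specific hazards.
3. Keep cholangiopathy-free survival as a descriptive composite, state which events it counts, and tabulate its components (IC, death, other graft loss) by graft type.

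The cost is wording in the outcome and analysis sections and a standard routine. Dates of death and retransplant are already needed for AF and survival. No extra patients or procedures are required.
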